### Criteria for discontinuing or modifying allocated interventions {11b}

Participants will be withdrawn from the trial if they are considered not suitable for non-competitive physical activity. The following criteria will be considered: disabling pneumological, cardiological, neurological, orthopedic comorbidities, or mental illnesses that affect the exercise performance; treatment with beta blockers, non-dihydropyridine calcium channel blockers, or amiodarone due to their potential effect on heart rate response to exercise; treatment with antidepressant drugs; and recurrence diagnosis.

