### Relevant concomitant care permitted or prohibited during the trial {11d}

Information on concomitant medication (prescription, over-the-counter, herbal and naturopathic remedies, etc.) will be collected at the beginning and during the study.

The research team will not interfere with the medication prescription, which will be chosen by the health care providers (i.e., oncologist and general practitioner). If the concomitant medications are incompatible with the inclusion criteria of the study, the participants will be excluded from the study.

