Secondary outcome measure:2.Fatigue: change in fatigue perception assessed by the brief fatigue inventory (BFI) questionnaire. The score of the questionnaire ranges from 0 to 90. A higher score means more severe fatigue.3.Anthropometry: change body mass index (BMI) expressed as kg/m^2^.4.Body composition: change fat mass (%) assessed by bioelectrical impedance analysis.5.Cardiac function indexes: change in the global longitudinal strain (%) assessed by echocardiography.6.Heart rate variability: change in heart rate variability assessed by 24-Holter monitoring.7.Cardiorespiratory fitness: change in cardiorespiratory fitness assessed by estimated maximal oxygen uptake (mL/min/kg).8.Flexibility: change in muscle flexibility assessed by sit and reach test (m).9.Muscular fitness: change strength assessed by isometric hand grip strength test (kg).10.Proprioceptive recalibration: change assessed by stabilometry (mean velocity) (mm^2^/s^2^).11.Posture balance: change assessed by stabilometry (Romberg Quotient test-European variant) (% over or under 100).12.Upper limb muscle viscoelastic characteristics: change in the muscle properties of the pectoralis major, upper trapezius, and sternoclavicular mastoid muscle assessed by a hand-held myotonometer.13.Psychological well-being: change in mood profile assessed by the Profile of Mood States (POMS) questionnaire. The POMS questionnaire gives a 5-point Likert scale; a higher score indicates increased negative mood.14.Homeostatic Model Assessment for Insulin Resistance (HOMA-IR) Index: change in HOMA-IR Index calculated as HOMA-IR = (FPI × FPG)/22.5, where FPI is fasting plasma insulin concentration (mU/L) and FPG is fasting plasma glucose (mmol/L), or as HOMA-IR = (FPI × FPG)/405 if fasting plasma glucose is expressed in mg/dL.15.Insulin-like growth factor (IGF-1): change in IGF-1 assessed by blood samples (μg/L).16.C-reactive protein: change in high sensitivity C-reactive protein assessed by blood samples (mg/L).17.Gut microbiota: change in microbial diversity (species diversity %) assessed by next-generation sequencing (NGS) of the V3–V4 region of the 16S rDNA gene.18.Osteoporosis level: change in computerized bone mineralometry assessed by *T*-score (normal: +2.5> *T*-score > −1.0; osteopenia: −1.0> *T*-score >−2.5; osteoporosis: *T*-score <−2.5; severe osteoporosis: *T*-score <−2.5 with one or more fragility fractures).19.Recurrences: recurrence-free interval defined as the time from registration to the time of documented recurrent disease.

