### Methods in analysis to handle protocol non-adherence and any statistical methods to handle missing data {20c}

This study will employ a per-protocol analysis in which missing data will not be imputed. Sensitivity analyses will be performed to assess the robustness of the results based on quantitative and qualitative levels of adherence to the exercise protocol. The main statistical analyses will be performed without considering the exercise protocol adherence. In accordance with the available literature (see Hawley-Hague et al. [31] for a methodological review on this topic), the three sensitivity analyses will be performed by including, in the statistical analysis, only the participants who completed at least 65, 70, and 75% of the total training sessions exercising at both the prescribed intensities (i.e., with an average exercise intensity of each session within 4 bpm of the prescribed HR [21]) and durations (i.e., with an exercise session duration within 5 min of the prescribed duration). The qualitative reasons for withdrawal from the trial or non-adherence to the exercise protocol will be recorded. Finally, to assess if the missing data and non-adherence to the exercise protocol are at random, exploratory analyses will be performed to assess the presence of patterns among the missing data, exercise protocol non-adherence, participants’ characteristics, and group allocation.

Trial retention will be scored as the rate of drop-out in the intervention group after signing informed consent for the study.

Cohort retention drop-out in the intervention and control group will be defined as withdrawal from the cohort and/or non-response to the regular cohort measurements and will be scored for both groups.

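### Stopping the training and leaving the trial are merged, so outcome follow-up ends after randomisation for events plausibly tied to quality of life

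*Protocol article*

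**What the plan says.** The rule in {11b} is: "Participants will be withdrawn from the trial if they are considered not suitable for non-competitive physical activity". It speaks of participants and not of the training arm, so it also covers control women, who have no sessions to stop. The criteria are of three kinds:

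- illness, worded as "disabling pneumological, cardiological, neurological, orthopedic comorbidities, or mental illnesses that affect the exercise performance"
- use of any of a short list of named drugs that can change how heart rate responds to effort
- two further grounds, worded as "treatment with antidepressant drugs; and recurrence diagnosis"

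Section {11d} records medication at the start and during the study, and adds: "If the concomitant medications are incompatible with the inclusion criteria of the study, the participants will be excluded from the study".

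On analysis, {20c} says: "This study will employ a per-protocol analysis in which missing data will not be imputed". It also says: "The main statistical analyses will be performed without considering the exercise protocol adherence". Reasons for withdrawal are recorded, and patterns of missing data are explored.

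The primary outcome in {12} is change in the EORTC QLQ-C30. Mood (POMS) is secondary, and so is the "recurrence-free interval defined as the time from registration to the time of documented recurrent disease". Follow-up runs to 24 months. No section says that outcomes are still collected after a withdrawal under {11b} or {11d}. Section {22} follows up only adverse events.

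**The concern.** Two decisions are treated as one. Whether a woman goes on training is a clinical matter. Whether her outcomes go on being measured is a matter of trial validity. The heading of {11b} concerns the first; its text decides the second.

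The triggers are not neutral. Starting an antidepressant, developing a mental illness, becoming disabled by a comorbidity and having a recurrence all plausibly go with poor QoL or mood. If women leave measurement at that moment, those who remain look better than the arm as randomised. The comparison is distorted whenever the two arms lose different numbers of such women, or women with different deficits. The intervention may itself change how often the events occur, so equal loss cannot be taken for granted. The Discussion says the trial wants drop-out not to be affected by the study design, yet this rule makes some drop-out part of the design.

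**Working it through.** **1. The plan's own figure.** Inputs from {14}: expected change 15.1 (SD 17.7) with intervention and 6.1 (SD 17.1) with control, alpha 0.05 (two-sided per {20a}), power 0.80.

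- Planned difference: 15.1 − 6.1 = 9.0.
- Pooled SD: √((17.7² + 17.1²)/2) = 17.40.
- n per group: 59 by the normal approximation, 60 by the noncentral t (power 0.802). The stated 60 is reproduced.
- Inflation for 30% drop-out: 120/0.7 = 171.4, rounded up to 172. Also reproduced.

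The 30% allowance keeps the numbers up. It does nothing about who is lost.

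**2. Bias from outcome-related loss.** Let a share w of an arm be withdrawn, with a mean QoL change D points worse than that of women who stay. If the full-arm mean is μ and the mean of those who stay is m, then μ = (1 − w)m + w(m − D), so m = μ + wD. With the same D in both arms:

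observed difference = 9.0 + D × (w_int − w_ctrl)

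The documents give neither w by reason nor D, so all values below are assumptions.

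| Difference in withdrawal between arms | D | Bias, points | Share of 9.0 |
|---|---|---|---|
| 5 percentage points | 10 | 0.5 | 6% |
| 5 | 20 | 1.0 | 11% |
| 10 | 10 | 1.0 | 11% |
| 10 | 20 | 2.0 | 22% |

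The sign follows the arm that loses more. With D = 20:

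- control 10%, intervention 5%: 9.0 − 1.0 = 8.0
- control 5%, intervention 10%: 9.0 + 1.0 = 10.0
- 5% in both arms: 9.0, although each arm mean is then 1.0 too high

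As a more extreme case, control 15%, intervention 5% and D = 30 gives 9.0 − 3.0 = 6.0.

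**3. Against sampling error.** The planned standard error is √((17.7² + 17.1²)/60) = 3.18. A bias of 0.5 to 2.0 points is 0.16 to 0.63 of it. If the expected difference fell from 9.0 to 7.0, power at 60 per group would fall from about 0.80 to about 0.59.

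**4. Can other sections restore the data?** Ignoring adherence in the main analysis ({20c}) concerns training sessions; it cannot bring back questionnaires that were never given. Recording reasons and exploring missingness patterns is diagnostic, not corrective. Analysing women as randomised would not help either if their outcomes were not collected.

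**5. Recurrence.** When a recurrence triggers withdrawal, the event of the recurrence-free interval has already occurred and can be counted if documented. Two things are lost: later QoL in those women, and later recurrences in women withdrawn earlier for a drug or a comorbidity, whose censoring may be informative.

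**The case against.** The case against has several sound parts.

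- **Recurrence events.** A reader might infer that the rule deletes recurrences from the recurrence results. The documents do not support that: the recurrence is the endpoint itself, and withdrawal follows it.
- **Breadth of the criteria.** A reader might take any new comorbidity as a trigger. The text requires it to be disabling and to affect exercise.
- **Uneven detection.** A reader might infer that the trained arm, seen twice weekly with heart-rate monitors, must show more withdrawals. This is only partly supported. Medication recording ({11d}) and psychological evaluation ({11a}) apply to both arms. At most, closer contact might bring exercise-limiting conditions to light sooner.
- **Size.** The primary comparison spans about 12 weeks, in women already screened for most of these conditions at entry. A 10-point gap in withdrawal would mean about 9 extra women in an arm of 86 (0.10 × 86 = 8.6). The bias may be small at that point.
- **Beyond repair.** It is too strong to say that no model could correct the loss. Reasons are recorded, and an adjustment is possible, but it would rest on assumptions that the remaining data cannot test.
- **Overlap.** Part of the harm to QoL runs through the per-protocol rule in {20c}, so the two should not be counted twice.

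It can also be argued that {20c} separates trial retention from cohort retention, so that women who leave the trial might still be measured, and that such detail belongs in the full protocol. This does not rescue the plan. No section says that withdrawn women stay under measurement, and the article states the opposite rule affirmatively in {11b} and again in {11d}.

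**Conclusion.** The point holds as a should-fix. Followed as written, {11b} and {11d} end participation in either arm for events several of which are plausibly tied to QoL and mood, and {20c} offers nothing in place of the lost outcomes. The 0.5 to 2.0 points rest wholly on assumed withdrawal differences and deficits, with the same deficit in both arms. The direction is unknown, so the documents do not support saying that the rule favours or disfavours exercise. The problem is likely to matter more at 12 and 24 months, when such events have accumulated, than at 12 weeks. The planned sample size is unaffected.

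**What to change.** Reconcile the heading of {11b} with its text and with {11d}, leaving the clinical criteria for stopping training unchanged. State that:

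- meeting a criterion does not end outcome follow-up;
- the QLQ-C30, the mood questionnaire and recurrence status continue at the scheduled visits for all randomised women unless consent is withdrawn;
- the event and its date are recorded;
- the data are analysed in the arm assigned.

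The cost is an ethics amendment with re-consent, as the section on amendments ({25}) requires, and a few extra questionnaires at visits that already exist. Recruitment began in January 2020, so data from women already withdrawn may not be recoverable; their number, arm, reason and date should be reported.

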### Strategies to improve adherence to interventions {11c}

Before the intervention phase, motivational interviews will be organized. These meetings will be structured in 15 min of personalized interviews in which the nutritionists and exercise specialists explain the oncological lifestyle recommendations based on the WCRF 2018 and the recent guidelines on nutritional and exercise for breast cancer patients, approved by the Ministry of Health 2017 and 2019 [8, 13, 20, 23].

At each follow-up, the patient will be able to fill in specific questionnaires about nutrition and exercise to assess adherence to lifestyle changes.

### Relevant concomitant care permitted or prohibited during the trial {11d}

Information on concomitant medication (prescription, over-the-counter, herbal and naturopathic remedies, etc.) will be collected at the beginning and during the study.

The research team will not interfere with the medication prescription, which will be chosen by the health care providers (i.e., oncologist and general practitioner). If the concomitant medications are incompatible with the inclusion criteria of the study, the participants will be excluded from the study.

### Provisions for post-trial care {30}

At the end of the trial, participants will continue to follow the standard of care within the Clinical oncology Unit involved in the project.

### Outcomes {12}

Primary outcome measure:Quality of life assessed by questionnaire: change in the quality of life assessed by the European Organisation for Research and Treatment of Cancer Quality of Life Questionnaire (EORTC QLQ-C30). Scores ranging from 0 to 100; higher scores indicate better quality of life.

Secondary outcome measure:2.Fatigue: change in fatigue perception assessed by the brief fatigue inventory (BFI) questionnaire. The score of the questionnaire ranges from 0 to 90. A higher score means more severe fatigue.3.Anthropometry: change body mass index (BMI) expressed as kg/m^2^.4.Body composition: change fat mass (%) assessed by bioelectrical impedance analysis.5.Cardiac function indexes: change in the global longitudinal strain (%) assessed by echocardiography.6.Heart rate variability: change in heart rate variability assessed by 24-Holter monitoring.7.Cardiorespiratory fitness: change in cardiorespiratory fitness assessed by estimated maximal oxygen uptake (mL/min/kg).8.Flexibility: change in muscle flexibility assessed by sit and reach test (m).9.Muscular fitness: change strength assessed by isometric hand grip strength test (kg).10.Proprioceptive recalibration: change assessed by stabilometry (mean velocity) (mm^2^/s^2^).11.Posture balance: change assessed by stabilometry (Romberg Quotient test-European variant) (% over or under 100).12.Upper limb muscle viscoelastic characteristics: change in the muscle properties of the pectoralis major, upper trapezius, and sternoclavicular mastoid muscle assessed by a hand-held myotonometer.13.Psychological well-being: change in mood profile assessed by the Profile of Mood States (POMS) questionnaire. The POMS questionnaire gives a 5-point Likert scale; a higher score indicates increased negative mood.14.Homeostatic Model Assessment for Insulin Resistance (HOMA-IR) Index: change in HOMA-IR Index calculated as HOMA-IR = (FPI × FPG)/22.5, where FPI is fasting plasma insulin concentration (mU/L) and FPG is fasting plasma glucose (mmol/L), or as HOMA-IR = (FPI × FPG)/405 if fasting plasma glucose is expressed in mg/dL.15.Insulin-like growth factor (IGF-1): change in IGF-1 assessed by blood samples (μg/L).16.C-reactive protein: change in high sensitivity C-reactive protein assessed by blood samples (mg/L).17.Gut microbiota: change in microbial diversity (species diversity %) assessed by next-generation sequencing (NGS) of the V3–V4 region of the 16S rDNA gene.18.Osteoporosis level: change in computerized bone mineralometry assessed by *T*-score (normal: +2.5> *T*-score > −1.0; osteopenia: −1.0> *T*-score >−2.5; osteoporosis: *T*-score <−2.5; severe osteoporosis: *T*-score <−2.5 with one or more fragility fractures).19.Recurrences: recurrence-free interval defined as the time from registration to the time of documented recurrent disease.

Other pre-specified outcome measures:20.Diet habits: change in dietary intake assessed by questionnaire (14-item Mediterranean diet adherence screener, MEDIET) through the DIANAWeb platform. Higher levels (8–9 or >10 points in the 14-item score) indicate adherence to the Mediterranean diet.21.Physical activity level: change in physical activity level assessed by the sensewear armband activity monitor and by the international physical activity questionnaire (IPAQ). The output of both assessments expressed in metabolic equivalents (METs)-min/week.

### Participant timeline {13}

The participant timeline is presented in Fig. 1.

**Fig. 1 Fig1:**
[figure not shown]
Project timeline. Schedule of enrolment, intervention, and list of assessments across the study timepoints

### Sample size {14}

The sample size was calculated with the aim of verifying the differences between the QoL changes in the two groups (i.e., intervention and control arm), after 3 months of intervention.

The QoL expected improvement in the experimental group at 12 weeks is 15.1 ± 17.7, while in the control arm, it is 6.1 ± 17.1 [24]. Using a *t*-test for independent samples, with an alpha of 0.05 and statistical power of 0.80, to find differences in QoL improvements between the two groups at the end of the intervention, 60 participants per group will be needed. Considering an expected drop-out of 30%, a total of 172 patients will be recruited. The sample size was calculated using Stata statistical software (StataCorp. 2013. Stata Statistical Software: Release 13. College Station, TX: StataCorp LP).

### Recruitment {15}

During routine hospital visits, patients will be informed by the oncologist about the benefits of physical activity and nutrition for recurrence prevention and the MoviS trial will be presented in detail. In addition, the project will be promoted by social media and public events. Patients who wish to participate will be screened for the evaluations for the eligibility criteria.

## Assignment of interventions: allocation

### Sequence generation {16a}

In order to ensure balanced groups, participants will be randomized to the two arms (with a 1:1 ratio) using permuted block (*n* = 4) randomization, stratified according to the anthracycline treatment.

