### Concealment mechanism {16b}

Because randomization occurs using a digital tool, there is no human involvement, and the process is fully concealed from both study investigators and prospective participants until the study arm is assigned according to the 16a item.

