### Implementation {16c}

Participants will be enrolled by the oncologists of the Medical Oncology Unit of the Urbino Hospital (PU, Italy). The allocation to the intervention program will be randomly assigned by statisticians, who will be blinded to participants’ information. Randomization will take place using a manual list accessed electronically via Interactive Web Response System (IWRS) after randomization eligibility is determined (Fig. 1).

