## Assignment of interventions: blinding

### Who will be blinded {17a}

Patient allocation and intervention will not be blinded. The data collectors will be aware of the participants’ allocation during the physical fitness assessments (i.e., cardiorespiratory, muscular, and flexibility fitness), whereas the data collectors of the clinical, biological, and other outcomes are unaware of the participant’s allocation. However, data preparation, elaboration, and statistical analysis of primary and secondary outcomes will be performed by researchers and statisticians in a blinded manner.

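### A single fixed block size of 4 in an open-label, one-unit trial makes up to a third of allocations deducible, so the claim of full concealment is overstated

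*Protocol article*

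**What the plan says.** Under Sequence generation {16a} the protocol article states that "participants will be randomized to the two arms (with a 1:1 ratio) using permuted block" randomisation. It gives one block length, 4, and one stratifier: "stratified according to the anthracycline treatment". It mentions neither varying lengths nor withholding the length from enrolling staff.

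Under Concealment mechanism {16b} it argues that, because a digital tool is used, "the process is fully concealed from both study investigators and prospective participants until the study arm is assigned". Under Implementation {16c} the oncologists of one hospital unit enrol, and "The allocation to the intervention program will be randomly assigned by statisticians", who work from a list reached through an interactive web response system (IWRS) once eligibility is settled.

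Under Who will be blinded {17a}: "Patient allocation and intervention will not be blinded". Procedure for unblinding {17b} calls the design open-label, and the Discussion describes a single institution. Recruitment {15} has the oncologist present the trial at routine visits.

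**The concern.** Concealment has two parts. The list must be hidden, and the next entry must not be deducible from what is already known. An IWRS secures the first part only. With a constant block length, 1:1 allocation and open arms, the second part fails for anyone who knows the length and can follow earlier allocations in the same stratum. The treating oncologist can be expected to know a woman's anthracycline history, and therefore her stratum.

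The people who present the trial also enrol. If they could foresee the next arm, they could time the approach or entry of particular women, for instance those keener to exercise. The primary outcome is a self-reported quality-of-life questionnaire completed by unblinded participants, and the Discussion itself names motivation to change lifestyle as something that can shift behaviour. Analysing the change from T1 to T2 removes a simple difference in baseline level. It does not remove a difference in motivation that affects the change itself.

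**Working it through.** **Inputs.** Block length 4 and ratio 1:1 (Sequence generation {16a}). Total of 172 women (Sample size {14}). Two strata, assuming anthracycline treatment is coded yes/no. The article gives no figure for predictability. Its total is reproduced by 60 per group / 0.70 = 85.7, rounded up to 86, and 2 × 86 = 172.

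**Allocations known with certainty.** A block holds two places per arm, so there are 6 equally likely orders. In 2 of them (AABB, BBAA) the last two places are forced. In the other 4 only the last place is forced.

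- Forced places per block: (2×2 + 4×1)/6 = 1.333
- Share: 1.333/4 = 33.3%
- Applied to the trial: 172/3 = 57.3
- Simulation of 172 women in two strata, allowing for incomplete final blocks: 32.9%, or about 57 women. The result is the same with strata split 30/70 or 50/50.

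**Best guess.** Always name the arm with more places left, and toss a coin when they are equal.

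- Place 1: 1/2
- Place 2: 2/3
- Place 3: 1/3 × 1 + 2/3 × 1/2 = 2/3
- Place 4: 1
- Mean: (1/2 + 2/3 + 2/3 + 1)/4 = 17/24 = 70.8%, against 50% with no information

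**Alternatives.** Fixed lengths are enumerated exactly for complete blocks. Varying lengths are simulated with 86 women in a stratum and each length equally likely. The observer is allowed to know the set of lengths but not the length of any one block.

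| Scheme | Certain | Best guess right |
|---|---|---|
| Fixed 4 (the plan) | 33.3% | 70.8% |
| Fixed 6 | 25.0% | 68.3% |
| Fixed 8 | 20.0% | 66.6% |
| Random 4/6 | about 6% | about 69% |
| Random 4/6/8 | about 2% | about 68% |

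On the simulated basis the plan's fixed 4 gives 32.5% and 70.5%, so the comparison does not depend on the method. Varying the length nearly removes certain knowledge. It does little to the accuracy of an educated guess.

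**Imbalance.** An incomplete block of length b can leave the arms b/2 apart: 2 for a block of 4, and 4 for a block of 8. If a block of 4 is abandoned part-way at the switch, its imbalance of up to 2 can add to that, giving at most 4 + 2 = 6 per stratum.

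**The case against.** The strongest reply is that one third is a ceiling. It needs an enrolling oncologist who knew the block length at the time, saw every earlier allocation, and tracked them in order within each stratum. The document shows none of these. Section {17a} says that allocation is open, but not that oncologists see a running list ordered by stratum, and it keeps collectors of clinical outcomes unaware of the arm. Recruitment began in January 2020, so the article's printing of the block length cannot have informed enrolment before it appeared. All of this stands. A reader might infer that clinicians did know a third of the allocations in advance, but the document does not support that.

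A reader might also infer that {16b} and {16c} describe incompatible procedures, since one says "there is no human involvement, and the process is fully concealed from both study investigators and prospective participants" while the other has statisticians assign from a list. A list prepared by statisticians and released through an IWRS is ordinary practice, and the first sentence can be read as describing the release step. This is loose wording, not two rival methods.

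Finally, the bias is not sized. Entry is restricted to inactive women who meet risk criteria, some are reached through social media and public events, and the analysis uses change scores. These points limit the scope for steering but do not remove it. The remedy also barely changes guessing accuracy. That is true; its benefit is the loss of certainty, which is what would make steering reliable.

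**Conclusion.** The point holds as a design weakness and an overstated claim. Fixed blocks of 4 with open allocation and one enrolling unit permit up to one third of allocations to be deduced with certainty, and about 71% to be guessed correctly, by a person who knows the block length and keeps a tally within strata. The figure of about 57 of 172 further requires that this was done from the first patient. Using a digital tool does not rule this out, so full concealment does not follow from it.

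The result rests on reading n = 4 as the block length, which is the natural reading, and on two anthracycline strata. It does not show that any allocation was foreseen or that the quality-of-life comparison is biased, and the sample size is unaffected. A change is worth making because it is cheap and the primary outcome is self-reported.

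**What to change.** For all allocations still to be made, load into the existing IWRS a computer-generated list with randomly varying block lengths (for example 4, 6 and 8) within the anthracycline strata, and withhold the lengths from enrolling staff. Amend {16a} to say so, and state that earlier allocations used fixed blocks of 4.

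In {16b}, limit the claim to what the procedure delivers: the list is hidden and each allocation is released only after eligibility is confirmed. As a minor clarification, align {16b} with {16c} so that one description covers who prepares the list and how it is released.

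The cost is one new list and a short amendment. The possible imbalance per stratum rises from at most 2 to at most 4, or 6 if a block of 4 is left incomplete at the switch, which is small against 172. The change helps only women not yet randomised. The article puts the end of recruitment at about 31 May 2023 and does not say how many women remain. The corrected concealment statement is worth making in any case.
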